## 4. Ethics and dissemination

This study was approved by the Human Research Ethics Committee of Xinxiang Medical University [code: XYEFYLL-(Research)-2022-29] and the Human Research Ethics Committee of Universiti Sains Malaysia (code: USM/JEPeM/22080545). This study will abide by the ethical conduct of the Declaration of Helsinki 1964 and its subsequent amendments and also the Clinical Good Practice guidelines for clinical trial in Malaysia. The English and Chinese versions of the participant information sheet and consent form are included in Appendices 4, 5. A clinical trial monitoring committee will be set up which will be led by the principal investigator in coordination with the trial coordinator and field coordinator and will meet up every week to discuss, record, and report the day-to-day conduct of the clinical trial and audit of the trial which will be submitted to the human research ethics committee of both Xinxiang Medical University and Universiti Sains Malaysia. Auditing of the trial will be carried out by the Clinical Trial Coordination Unit of the Second Affiliated Hospital of Xinxiang Medical University and Advanced Medical and Dental Institute of Universiti Sains Malaysia and independent from the funder of the RCT. If there are any changes in the initial research protocol submitted (such as changes in the subject recruitment, data collection, and data analysis.), the changes will be reported to the Human Research Ethics Committee of both Xinxiang Medical University and Universiti Sains Malaysia.

The following information will be delivered to all participants before they are enrolled in the study:

The right of the participant to withdraw from the study at any time without the need to provide any reason and the data collected from them will be discarded and will not be used for the study.The anonymity of the participant is assured, and no personally identifiable information will be used for research purposes. For example, all participants will be provided with a research number for identification purposes, such as VT001 and VT002. The group data will be computed and reported as research findings instead of using individual data.The data collected will be stored in a research file which will be locked in a file cabinet where the key will be kept by the principal investigator. In addition, the data collected may also be stored in thumb drive which will be kept by the principal investigator. Only the research team members have access to the research file and thumb drive.The collected data may be stored for a duration of at least 2 years after completion of the study, and then, it will be discarded following the standard procedures. Any reuse of the data will need consent from the participants.The research team will only access the collected data for publication purposes and presentation in academic conferences or symposia. As for publication of the research findings, the principal investigator is the corresponding author while the other author arrangement will be decided based on the International Committee of Medical Journal Editors' recommendations. All the researchers declared that there is no competing interest in any financial gain or conduct of the study.

Adverse effect is any untoward event that occurred in relation to or not related to the interventions in the clinical trial. All participants will be given a clinical trial card which contains the full name, telephone number, and email of the person in charge of adverse effect reporting in the research team. All participants who experience any adverse effects are encouraged to contact the person in charge of the research team. All adverse effects have to be reported in the adverse effect section of the case report form, in which the following details need to be filled, such as the date and time of adverse effects occurrence, the duration, description of the adverse effects, treatment seek, time taken for adverse effects to resolve or still on-going. Participants who experience adverse effects will be withdrawn from the study. The events are considered adverse effects which lead to the withdrawal of participants from the study include the following:

Any adverse effect or reaction which is unrelated to the intervention under investigation in the study;Any adverse effect or reaction which is related to the intervention under investigation in the study, which occurred after the intervention is administered;Any adverse effect or reaction which leads to severe psychological distress, psychotic symptoms, change of behavior and personality, deliberate self-harm, or suicidal tendency;Any adverse effect or reaction which is suspected or unexpectedly associated with the intervention under investigation according to conventional practice.

All adverse effects need to be reported to the Human Research Ethics Committee of Xinxiang Medical University or Universiti Sains Malaysia. An interim analysis will be conducted to investigate the adverse effect reported in a clinical trial and if found to induce risk of morbidity or mortality and it is related to the intervention under investigation; then, the clinical trial will be terminated prematurely. Adverse effects which will lead to premature termination of the clinical trial include those that induce deliberate self-harm, suicidal tendency, and hospitalization of the participants. As for participants who reported serious adverse effects during post-trial, they will be referred to the nearest treatment facility for further treatment, and they will also be compensated if the serious adverse effect is related to the study intervention.

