### 2.8. Blinding

The researchers will be blinded in this study, in which the recruitment and randomization of the participants will be conducted by a research assistant not involved in this study. The data collection will also be carried out by another research assistant who is also not involved in the study and does not know the objectives of the study. A statistical analysis plan will also be prepared, and the statisticians who will analyze the data are also not part of the research team. The researchers will only be unblinded after the data analysis is completed. The researchers will be unblinded if serious adverse effects occurred in the participant which may or may not be related to the study intervention. The participants are not blinded due to significant differences in the features of the intervention group.

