### 2.9. Measures

This study follows the Standard Protocol Items: Recommendations for Intervention Trials (SPIRIT) 2013. The checklist for SPIRIT is included in Appendix 3. The schedule for assessments in this study is summarized in Table 1. There will be four timelines of assessment. Baseline assessment (t_0_) commences after the randomization of participants into the three intervention groups (VRET, ACT, and control groups), wherein the sociodemographic, clinical, and alcohol use characteristic questionnaire, Alcohol Use Disorder Identification Test (AUDIT), Penn Alcohol Craving Scale (PACS), Hamilton Anxiety Rating Scale (HAM-A), and Hamilton Depression Rating Scale (HAM-D) are administered, while event-related potential (ERP) detection in electroencephalogram (EEG) is performed in the participants. Then, during follow-up assessment, such as t_1_ = 4 weeks (immediately after completion of intervention), t_2_ = 12 weeks (8 weeks after completion of intervention), and t_3_ = 24 weeks (20 weeks after completion of intervention), the questionnaires are re-administered to the participants which include alcohol use characteristics, AUDIT, PACS, HAM-D, and HAM-A, while ERP detection in EEG is re-assessed. The serial assessments will be carried out by a research assistant who is not involved in the research project and does not know about the objectives of the study. The research assistant will receive some training on the administration of the measures before the data collection begins. To ensure that the participants complete the serial assessments and interventions, an appointment card is given to each participant with the next appointment date written on the card. Emails and messages will be distributed 3 days prior to the appointment to remind the participants regarding the appointment date, and if any participant does not reply, a phone call will be made a day before the appointment date.

**Table 1 T1:** Schedule of assessments of the study outcome measures.

	**Enrollment**	**Allocation**	**Post-allocation**		
**Time**	* **–t** _1_ *	***t**_0_* **(0 week)**	* **t** _1_ * **(4 weeks)**	***t**_2_* **(12 weeks)**	* **t** _3_ * **(24 weeks)**

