### 2.10. Data analysis

Data analysis will be carried out using the Statistical Package for Social Sciences version 26 (SPSS-26, Inc., Chicago, IL, USA). Descriptive statistics for sociodemographic, clinical, and alcohol use characteristics, AUDIT, PACS, HAM-D, and HAM-A scores, and ERP will be computed. For nominal and ordinal data, these will be presented in frequency and percentage. For continuous data, it will be presented as mean and standard deviation if the variable is normally distributed. While for non-normally distributed data, it will be presented as median and interquartile range. The normality of the data will be determined by Shapiro–Wilk test.

As for the assessment of the primary outcome, one-way ANOVA with false discovery rate adjustment is used to compare the mean of the outcomes (PACS, average number of drinks during drinking days, frequency of binge drinking in the previous week, and the number of hazardous drinks per day or per week) between the three groups (VRET, ACT, and control groups) at each specific time point (t_0_, t_1_, t_2_, and t_3_). While for the main analysis, mixed ANOVA is used to evaluate the interaction of intervention and time on the outcomes will be computed (outcomes: PACS, average number of drinks during drinking days, frequency of binge drinking in the previous week, and the number of hazardous drinks per day or per week; interaction: intervention × time; whereby time is the within-subject factor, while intervention is the between-subject factor). The main effect of the interaction will be presented as estimated marginal mean and standard error of mean. The primary outcome assessment will follow the intent-to-treat principle. The data analysis for the secondary outcomes (AUDIT, HAM-D, and HAM-A scores and ERP) will be analyzed in the same way as the primary outcomes. Statistical significance is set at *p* < 0.05 and is two-tailed.

As for the management of missing data, if there is only 5% of missing data or less, it will be ignored and data analysis will proceed. However, if the missing data are from 5 to 40% and are missing randomly, multiple imputations with restricted maximum likelihood estimates will be performed using Stata 15, to estimate the missing values. However, if the missing data are more than 40% or are completely randomly missing or non-randomly missing, data analysis of the remaining data will proceed, and the missing data issue will be reported under the limitation of the study (46).

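### The promise to discard all data of participants who withdraw conflicts with the intent-to-treat commitment for PACS; separately, any adverse event, even an unrelated one, ends study participation

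*Protocol article*

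**What the plan says.** **Discard rule.** Section 4 (Ethics and dissemination) lists what participants are told, introduced by "The following information will be delivered to all participants before they are enrolled in the study". The first item lets them withdraw at any time without giving a reason and adds that "the data collected from them will be discarded and will not be used for the study".

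**Analysis principle.** Section 2.10 (Data analysis) states: "The primary outcome assessment will follow the intent-to-treat principle". For missing data it plans imputation "if the missing data are from 5 to 40% and are missing randomly, multiple imputations". Where data are "non-randomly missing, data analysis of the remaining data will proceed"; the same applies above 40% missing. At 5% or less, missing data are ignored.

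**Timing.** Section 2.9 (Measures) says "There will be four timelines of assessment", and that the first of them, t0, "commences after the randomization of participants into the three intervention groups".

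**Adverse events.** Section 4 defines an adverse effect so that it includes events with no relation to the intervention. It says participants who have one are withdrawn from the study, and unrelated events come first in its list of grounds. It sets no severity threshold and does not mention continued assessment at t1, t2 or t3.

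**The concern.** Intent-to-treat means that everyone randomised is analysed in the allocated arm. The discard rule takes people out because of what they do after randomisation, together with PACS values already recorded. Imputation cannot bring them back, because no observed PACS remains to impute from.

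The exclusions need not be neutral. Section 2.8 (Blinding) says: "The participants are not blinded due to significant differences in the features of the intervention group". The arms also differ visibly: one involves exposure to drinking scenes and aversive scenes, another offers supportive sessions with a later choice of ACT or VRET. Withdrawal could therefore differ by arm and be related to craving, which is the primary outcome. The PACS comparison would then no longer be between the groups as randomised, and discarded data cannot be recovered at the analysis stage.

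The adverse-event rule adds avoidable loss. A minor unrelated illness during the 24 weeks would end participation, although the remaining visits are already scheduled.

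**Working it through.** **1. The text.** For a participant who withdraws after t0, intent-to-treat keeps the participant and the observed PACS, whereas section 4 removes both. No section limits the discard to later data, to withdrawal before randomisation, or to participants who ask for deletion.

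**2. Possible bias.** The documents give no rates, so every input here is an assumption: no true effect, PACS in SD units, correlation 0.5 between visits, withdrawal after t1, and a correlation r of 0.2 to 0.5 between the tendency to withdraw and t1 PACS. If a share p of an arm withdraws, the mean t1 PACS of those left moves by r × φ(z)/(1 − p), where z is the (1 − p) normal quantile.

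- p = 0.10: φ(z)/(1 − p) = 0.1755/0.90 = 0.195
- p = 0.20: 0.280/0.80 = 0.350
- p = 0.30: 0.348/0.70 = 0.497

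The t0, t2 and t3 means move by 0.5 times the t1 shift.

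| Withdrawal | r | Shift in t1 difference (SD) | Shift at t0, t2, t3 (SD) |
|---|---|---|---|
| 20% vs 10% | 0.2 | 0.2 × (0.350 − 0.195) = 0.031 | 0.016 |
| 20% vs 10% | 0.5 | 0.5 × 0.155 = 0.078 | 0.039 |
| 30% vs 10% | 0.2 | 0.2 × (0.497 − 0.195) = 0.060 | 0.030 |
| 30% vs 10% | 0.5 | 0.5 × 0.302 = 0.151 | 0.075 |

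The standard error of a two-arm difference at 40 per arm is √(1/40 + 1/40) = 0.224 SD, so every shift is below one standard error. If t0 and t1 are kept and t3 is imputed from them, simulation gives shifts of about 0 at both t1 and t3.

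**3. The tests the plan names.** The main analysis is the intervention × time term of a mixed ANOVA. One-way ANOVAs across three groups at each visit, with false discovery rate adjustment, support it. With the third arm also at 10% (assumed), simulation under the same inputs gives:

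- three-group ANOVA at t1, before adjustment: type I error about 5.5 to 9.0% (a second simulation gave 5.0 to 8.6%);
- intervention × time: about 4.7 to 5.9% (second simulation 5.0 to 5.5%).

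The interaction test is nearly unaffected because discarding moves t0 as well. The shift in change from t0 is zero at t2 and t3, and at t1 it is half the t1 shift, 0.016 to 0.075 SD.

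**4. Power.** The formula is λ = f²Nm/(1 − ρ), with df (k − 1)(m − 1) and (N − k)(m − 1), f = 0.13 and k = 3; ρ = 0.5 is assumed. With the plan's m = 5, power 0.80 needs 91 participants, or 93 in multiples of three. Multiplying by 1.3 gives 118.3 to 120.9, which reproduces the stated 120. With the four actual time points, power is 0.87 at 120 (λ = 0.0169 × 120 × 4/0.5 = 16.2) and 0.70 at 84 = 120 × 0.70 (λ = 11.4).

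**The case against.** **The effect on the main analysis is small.** This stands. Under the illustration the interaction test stays close to nominal, and nothing shifts if withdrawal is equal across arms and equally related to craving. Other withdrawal mechanisms could do more, but the documents give no basis for choosing one.

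**Loss of power.** A reader might infer that the discard rule costs the fall from 0.87 to 0.70. It does not. A withdrawer's later visits are lost whether or not the earlier ones are kept, and section 2.2 already allows for 30% dropout.

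**Dropout is not withdrawal.** A reader might also infer that everyone who stops attending is erased. Section 2.9.3.5 (Other measures) records dropouts and their reasons separately, and nothing says the discard rule covers them. Nor does the document say that it covers participants withdrawn for adverse events.

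**Keeping data may not help.** This stands in part. A conventional mixed ANOVA uses complete cases, so outside the imputation branch a participant with t0 and t1 but no t3 leaves the main analysis anyway. Kept values would still enter the t1 comparison. The fix must therefore cover the analysis as well.

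**It is consent text, and an analysis plan will follow.** The consent wording in Appendices 4 and 5 is not shown, and deletion might turn out to be only on request. As printed, though, the promise is unqualified, and an analysis plan cannot restore data that participants were told would not be used.

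**Conclusion.** The contradiction is real and rests on the text alone: the discard promise and the intent-to-treat commitment for PACS cannot both be carried out for a randomised participant who withdraws after t0. Confidence in this is high.

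Its size is unknown. Under the assumed differential withdrawal the t1 difference shifts by 0.03 to 0.15 SD. The t1 three-group test then runs at about 5.5 to 9.0% before adjustment, and the main test at about 5 to 6%. These figures show direction and order of magnitude and are not a forecast.

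The adverse-event rule is a separate, lesser point. It is stated clearly, but what happens to those participants' earlier data is not, and confidence in its consequences is moderate.

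The plan should be corrected. The demonstrated effect on the main analysis is too small to call the trial's conclusion unsafe.

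**What to change.** 1. **Section 4 and the consent form.** Keep and analyse data collected up to withdrawal unless the participant explicitly asks for deletion. Report deletion requests by arm. Honour the existing promise for participants who have already consented under it.
2. **Section 2.10.** Analyse retained partial data with the planned imputation or a likelihood-based mixed model, so that a complete-case mixed ANOVA does not drop them again.
3. **Adverse-event text in section 4.** Replace withdrawal from the study with discontinuation of the intervention, for events the clinical team specifies. Keep the t1 to t3 assessments for those who still consent, and state that their data are retained.

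**Cost.** A protocol and consent amendment at both ethics committees, after checking Appendices 4 and 5. It changes a commitment made to participants, so it can apply only to those who consent under the new wording. No visits are added, since t1 to t3 are already scheduled.

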## Ethics statement

The studies involving human participants were reviewed and approved by (1) Human Research Ethics Committee USM, Division of Research and Innovation (R&I), [name]. (2) Human Research Ethics Committee Xinxiang Medical University, Second Affiliated Hospital, Xinxiang Medical University, [name]. The patients/participants provided their written informed consent to participate in this study.
